
**Research Proposal**

---

Eleven patients suffering from rhabdomyolysis or myositis (muscle symptoms with increased creatine kinase levels) were shown to have a reduced anaerobic threshold and tended to have reduced maximal oxygen consumption ( $\dot{V}O_{2\max}$ ) when compared to controls [20]. Whether such changes occur in patients suffering from statin-induced myalgia remains unknown.

These same patients suffering from rhabdomyolysis or myositis also demonstrated an increased respiratory exchange ratio during exercise [20]. A similar increase in respiratory exchange ratio during exercise was observed in type 2 diabetes patients under statin therapy [21]. These data suggest impaired fatty acid oxidation and an increased dependence on carbohydrate metabolism while under statin therapy, although this has not been evaluated in patients suffering from statin-induced myalgia.

**Mechanisms of statin myotoxicity.** Hypotheses attempting to explain statin effects on skeletal muscle cells generally relate to events leading to rhabdomyolysis and focus on reduced levels of products of the HMG-CoA reductase pathway. The most commonly cited are deficiencies in cholesterol (affecting membrane fluidity and function), coenzyme Q10 (resulting in perturbed mitochondrial respiration), and prenylated protein abnormalities (affecting intracellular protein messaging). Data supporting these hypotheses largely come from studies on cell culture or animal models of acute overdose [22]. Few data are available from human muscle biopsies, notably in relation to statin-induced myalgia.

Evidence from a small group of patients suffering from statin-induced rhabdomyolysis support effects of statins on skeletal muscle through prenylated protein anomalies. Phillips *et al.* [23] showed a tendency for elevated mRNA levels of the muscle atrophy signal atrogin-1 (which can be induced by reduced prenylation of G-proteins) and significantly decreased protein levels of the prenylated protein Ras. Although a number of histological and ultrastructural markers were also shown to be present in patients suffering from rhabdomyolysis, these were no more frequent than in age-matched controls. No differences in mitochondrial content, enzyme activities, muscle coenzyme Q10 concentrations or cholesterol levels were seen between groups. Limitations of this study include the absence of data on any changes to these parameters after statin withdrawal. Also, the inclusion of subjects from an age range reaching well into the late 80's (mean 64 yrs, range 49-87) is a potential confounder, since an acceleration of the loss of muscle function (*e.g.*, strength) is observed around 60 years of age (discussed in [24]).

The only data we are aware of that examined histological changes in muscle biopsies from patients with statin-related myalgia are from Phillips *et al.* [13]. In a very small group of only 4 patients, evidence of myocyte damage or mitochondrial dysfunction was observed that included abnormally increased lipid stores, fibers that did not stain for cytochrome oxidase activity, and ragged red fibers. These observations were reversible in 3 of the 4 patients following statin withdrawal within 2 months.

***These data support the hypothesis that changes at the level of the skeletal muscle cell, in particular in terms of mitochondrial structure and metabolic function, could be associated with statin-induced MRSE. Whether they precede or result from statin use remains unclear.***

**Vitamin D deficiency and myalgia.** Vitamin D deficiency is highly prevalent worldwide and low serum levels of 25-hydroxyvitamin D (25(OH)D) are associated with higher risk of cardiovascular morbidity and mortality [25]. Vitamin D deficiency is also associated with a number of muscle symptoms, *e.g.*, myalgia strikingly similar to that resulting from statins [26], and has also been associated with myositis [27]. Vitamin D insufficiency is highly prevalent in patients with type 2 diabetes and may cause neuropathic pain in the inadequate (serum 25(OH)D levels of 40–60 nmol/l) rather than severely deficient range (25(OH)D <30 nmol/l) [28].

**Vitamin D and muscle morphology and performance.** Effects of vitamin D levels on muscle performance have been reported in a few studies, vitamin D possibly improving muscle strength and function through a highly specific nuclear receptor in muscle tissue. Studies showing associations between vitamin D status and physical performance walking speed, sit-to-stand times, handgrip strength,

---

**Research Proposal**

---

and risk of falls are mostly observational and in older adults (reviewed in [29-33]). At the muscle cell level, vitamin D deficiency is associated with predominantly type II muscle fiber atrophy (more so in severely deficient patients), enlarged interfibrillar spaces and fat infiltration, fibrosis and glycogen granule accumulation [34].

Whether vitamin D supplementation can itself impact muscle strength or endurance or correct modifications observed with deficiency remains a matter of significant controversy. Studies into this area have mostly been performed in elderly patients, in the context of age-related sarcopenia or functional loss, and in the vast majority of cases with concurrent calcium supplementation. A number of studies have reported positive functional impacts of vitamin D supplementation on physical performance and risk of falls in the elderly, as reviewed in [29].

Only two studies have to our knowledge examined the effects of vitamin D supplementation on muscle morphology, both in patients with low vitamin D status. In a small, uncontrolled study, *vastus lateralis* biopsies before and after 3-6 months of 1-alpha-hydroxyvitamin D and calcium supplementation were recovered from elderly women suffering from bone loss [35]. Increased succinate dehydrogenase activity, phosphagen levels, as well as an increase in type IIA fiber proportion (at the expense of IIX fibers) and cross-sectional area were noted after the supplementation period. A randomized controlled trial in elderly women with post-stroke hemiplegia (48 supplemented, 48 placebo) taking 1000IU/day of vitamin D2 over 2 years resulted in increased type II fiber diameter and proportion as well as improved muscle strength in the vitamin D-treated group [36]. Positive correlations between type II fiber area and serum 25(OH)D levels were noted before and after treatment in this study. Increased type II fiber area is proposed to account at least in part for increased strength in these studies. However, whether these changes to fiber morphology resulted from direct effects of vitamin D on muscle cells remains unknown, as do the effects of vitamin D supplementation in patients with adequate or normal vitamin D status.

***Although these data suggest that vitamin D supplementation could lead to skeletal muscle morphology or functional changes, these changes are modest and would only be beneficial to patients suffering from statin-induced MRSE.***

**Vitamin D and statins.** The relationship between statins and vitamin D metabolism is not well-understood, although 7-dehydrocholesterol is the synthetic precursor of both cholesterol and vitamin D. Whether vitamin D insufficiency potentiates statin-induced myalgia, and whether statins contribute to vitamin D deficiency (in the circulation or at the tissue levels), is still poorly documented. The latter seems unlikely as atorvastatin and rosuvastatin treatments have been shown to increase serum 25(OH)D and active hormone 1,25-dihydroxyvitamin D concentrations [37, 38]. Wu-Wong *et al.* [39] showed that statins do not directly activate the vitamin D receptor *in vitro*, although it still remains to be determined whether some metabolites of statins could.

Vitamin D deficiency could itself impact statin metabolism. Simvastatin, lovastatin and atorvastatin are substrates of CYP3A4, the latter also displaying 25-hydroxylase activity *in vitro* [40]. In addition, CYP3A4 expression is also regulated by the vitamin D receptor pathway in at least some human tissues [41]. Vitamin D deficient states could thus lead to preferential shunting of CYP3A4 for hydroxylation of vitamin D, resulting in reduced availability of CYP3A4 for statin metabolism, contributing to statin-induced toxicity by increasing circulating drug concentrations. In agreement with this hypothesis, vitamin D supplementation (800 IU/day for 6 weeks) increased vitamin D-25-OH metabolites while reducing atorvastatin active metabolite concentrations in a trial including 16 men and women [42].

Clearly a complex interplay between vitamin D and statins occurs. Further studies are required to clarify the relationship between vitamin D deficiency and statin-induced myopathy and to confirm whether vitamin D repletion might resolve myalgic symptoms and allow statin reintroduction in a wide range of patients.

### Research Proposal

Early evidence does support a role for vitamin D supplementation in reducing statin-induced MRSE. Recent data from non-controlled trials show reversible myositis-myalgia in statin-treated patients receiving vitamin D repletion [43, 44]. In the study of Ahmed *et al.* [43], a greater proportion of statin-using patients with myositis-myalgia (64%) were found to have low levels of 25(OH)D when compared to asymptomatic statin users (43%). In this study, 38 vitamin D deficient myalgic statin-taking patients were supplemented with vitamin D (50,000IU/week for 12 weeks), resulting in increased serum vitamin D levels as well as resolution of myalgia in 92% of the cases. In the study of Lee *et al.* [44], 6 vitamin D deficient patients who had developed myopathy following statin introduction agreed to be rechallenged with statin therapy (same statin) following vitamin D supplementation, consisting of oral vitamin D3 doses of 1,000 – 10,000 units/day. Following repletion to reach normal 25(OH)D levels ( $84.5 \pm 7.5$  nmol/l), in four of these patients statin reintroduction was tolerated for at least 6 months without recurrence of myalgia. Notably, statin rechallenge was more likely to be successful in patients who achieved the highest post-treatment 25(OH)D levels ( $>80$  nmol/l). ***This suggests that achieving higher levels of serum 25(OH)D, even well above the currently proposed desirable level threshold of 75 nmol/l, might be beneficial in protecting against statin-induced myalgia.***

According to recent data from the Canadian Health Measures Survey of 2007-2009 and as analyzed by Statistics Canada [45], well over half (~55-65%) of Canadian adults (men and women) aged 40-79 years did not reach desirable 25(OH)D levels of 75 nmol/l. ***This would suggest that a large majority of Canadians under statin treatment has vitamin D metabolite levels well below those proposed by Lee *et al.* [44] and that vitamin D supplementation may help to alleviate drug-induced myalgia.***

### 3.0 STUDY DESIGN AND EXPECTED FINDINGS

A flow diagram summarizing the study design and an outline of patient participation can be found in **Figure 1** and **Table 1**.

[figure not shown]

**Figure 1:** Simplified timeline and flow diagram of proposed study. Q1, Q2, and Q3: questionnaires; Exam: physical examination (including anthropometry) and blood work; FT: functional muscle testing; Bx: *vastus lateralis* muscle biopsies (in a subset of patients).

**Table 1:** Subject population breakdown in proposed study. Subjects from objective #1 will be randomized into experimental (vitamin D) and control (placebo) groups for objective #2 based on age, sex, MRSE and 25(OH)D levels.

| Group                      | Objective #1          | Objective #2                                                     |
|----------------------------|-----------------------|------------------------------------------------------------------|
| Statin taking with MRSE    | 60 (20 with biopsies) | 30 vitamin D (10 with biopsies)
30 placebo (10 with biopsies) |
| Statin taking without MRSE | 30 (10 with biopsies) | 15 vitamin D (5 with biopsies)
15 placebo (5 with biopsies)   |
| Controls (no statins)      | 10 (5 with biopsies)  | —                                                                |

**Inclusion criteria:** Healthy and sedentary or moderately physical active (less than 1 hour of leisure-time physical activity per week) men and women aged 30 to 60 years (inclusive). Patients placed on statin therapy for the first time in the last year with or without MRSE and with normal CK blood levels.

**Exclusion Criteria:** Previous use of statins (before the last year); Current treatment with other lipid-lowering drugs; Natural medicine affecting lipid metabolism; Creatine kinase (CK) levels above the normal range (>180 U/L for women; >250 U/L for men); Clinical vitamin D deficiency (25(OH)D levels below 12.5 nmol/L); Impaired liver or kidney function; Untreated hypo- or hyperthyroidism; Treatment with other medications known to increase risk of myopathy in statin-treated patients (cyclosporine, anti-protease, azole antifungals...); Existing infection requiring antibiotic therapy; Consumption of greater than 60 ml of grapefruit juice per day; Inherited muscle disorders or myopathy; Polymyositis or inflammatory myopathy; Use of corticosteroids; Comorbidities resulting in muscle or bone pain (fibromyalgia, arthritis, sensory or intrinsic neuropathy, vertebral disease, loss of reflexes, muscle group atrophy); History of elevated CK (known or unknown etiology); Unexplained cramps; Known sickle cell trait; Cancer within the 5 years prior to study entry; Diabetes; Stroke, coronary artery or peripheral vascular disease; Physical disability or previous injury interfering with exercise testing; Pregnant or breastfeeding; Depression (in last 3 years) or treatment with antidepressants; Use of anti-psychotic drugs; Alcohol abuse.

**Power calculations.** Group sizes are derived from power calculations for changes in objective measures of muscle function as described in **Appendix 2**.

***OBJECTIVE #1: To test muscle strength and fatigability and investigate skeletal muscles at the histological and molecular levels in statin treated patients with and without MRSE***

**Subjects.** Men and women aged between 30-60 years (inclusive) and affiliated with the cardiovascular prevention lipid clinic at the CHUL will be included in this study. Only patients placed on statin therapy for the first time in the last year with or without MRSE (self-reported and assessed by questionnaires) and with normal CK blood levels will be recruited. These patients must never have taken statins or lipid-lowering drugs before the last year or consume vitamin D supplements, and their MRSE must clearly have begun after statin introduction. These patients will be in low cardiovascular risk primary prevention, allowing us to modify their lipid-lowering drug regimen for a short period of time. Informed written consent, to be approved by the CHUL ethics committee, will be obtained from each subject before entering the study. The lipid clinic at the CHUL is one of the largest in Canada, over 6000 patients seen or followed each year. The vast majority (estimated at 85-90%) of these patients are prescribed statins, and based on the personal experience of doctors at the clinic roughly 10% of these present symptoms of MRSE. A survey of patient records at the CHUL lipid clinic from June 2010 to February 2011 reveal nearly 300 patients with MRSE in our age range. Thus, we do not anticipate any need to recruit from other centers or through the media to reach our subject number goals, but these options remain available to us should they be required.

An extended screening profile for exclusion of inflammatory and metabolic myopathies will be performed. It is important to note that initial 25(OH)D levels will not be used as a criterion for subject recruitment (except for clinical vitamin D deficiency defined in our exclusion criteria). Vitamin D status (serum 25(OH)D levels), in addition to supplementation itself (in objective #2), will instead be assessed as potential contributors to improve statin tolerance in post-study statistical analyses.

One hundred (100) patients will be recruited for objective #1 (60 with MRSE, 30 without MRSE and 10 controls) for muscle function testing and a subset of 35 of them will also be investigated by percutaneous muscle biopsies. Ninety patients will be randomly distributed for objective #2 (60 with

---

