**Functional assessment and blood samples**

A case-control approach will be used to compare patients under statin treatment with and without MRSE. After initial testing while under statin treatment, statin treatment will be stopped for 2 months followed by retesting. Recent studies have shown that most statin MRSE as well as structural muscle damage appearance/disappearance occurs within a two month period of statin introduction/withdrawal [1, 13]. A control group of 10 statin-naïve patients will also be included for test-retest variability assessment of all parameters.

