Following screening, 60 patients presenting MRSE (assessed by a standardized questionnaire; see **Appendix 3, questionnaire 3**) under statin monotherapy (any statin, any dosage) as well as 30 patients without MRSE under statin monotherapy (paired for statin and dosage with the MRSE cohort) will be evaluated. Muscle strength and fatigability will be tested by standardized procedures before and after two months of stopping statin monotherapy. Briefly, strength of the extensors and flexors muscles of the dominant leg will be quantified with a Biodex isokinetic dynamometer available in our research centre. Forces will be tested during 3 reps at 60 and 180 deg/sec and endurance during a 15 reps test at 180 deg/sec. These tests will be preceded by a 5 reps warm-up at 60 deg/sec including one movement at maximal voluntary contraction [46]. Each maximal concentric contraction will be performed in the first 90 degrees of the knee range of motion. Patients will sit in an upright position and mechanical axis and resistance pads will be aligned according to the manufacturer's guidelines. The results will be reported in Newton-meters (Nm). Peak torque, rate of torque development and total work values will be obtained following these isometric and isokinetic measurements. These groups of muscles were selected because muscle weakness or myalgias with statins are most frequently localized in lower limbs. Handgrip strength of the dominant hand will also be tested in a static mode with a Jamar dynamometer (best of 3 repetitions). These testing procedures are well standardized, easy to perform and very reproducible, and are routinely used in the department of physical therapy at our centre. Test-retest variability for the Biodex measurements is shown to be within  $\pm 15\%$  [46], which our personal experience confirms. The primary efficacy parameter will be the percent change for these measurements from baseline to end of each phase of the study.

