In the experimental group (n=45; 30 with MRSE under statin monotherapy, 15 without MRSE under statin monotherapy from objective #1), statins will be reintroduced following one month of oral vitamin D supplementation (Vitamin D3 [cholecalciferol], Laboratoire Riva Inc., Blainville, Québec; 4 x 10,000 IU/week, 40,000 IU/week total). This falls within the range of average daily dosage used in the studies of Lee *et al.* [44] and Ahmed *et al.* [43] that showed relief from myalgia and allowed statin reintroduction in patients with low serum 25(OH)D levels. This also falls within the generally acceptable upper limit of daily vitamin D intake, the “no observed adverse event level” being 10,000 IU per day, and well below the “lowest observed adverse event level” of 40,000 IU per day (as discussed in [45]). Patients will be rechallenged with the same statin and at the same dose they were taking at the onset of objective #1. Patients will continue to supplement with vitamin D during the statin rechallenge period, which will last for a maximum of 2 months. The patients may request at any time over this period the cessation of statin therapy if they consider any reappearance of MRSE to be too severe to continue. Based on the clinical experience of [name] (co-PI), patients rarely develop muscle symptoms in less than 2 weeks following statin introduction.

In the control group (n=45; 30 with MRSE under statin monotherapy, 15 without MRSE from objective #1), no vitamin D supplementation will take place prior to statin reintroduction, subjects receiving instead a placebo provided by the pharmacy service of the CHUL. Placebo supplementation will also continue following statin reintroduction (1 month after the start of the RCT). Readers are referred to figure 1 and table 1 for more details on patient assignment.

Participants will be asked by the study coordinator, by phone, a few days before their visits at 4 weeks after randomization and at end-of-trial, to bring their bottles of capsules for their visit to the CHUL. The pharmacy will then check their apparent compliance by counting the remaining capsules and surveying the participants on their supplementation practices. A compliance rate of at least 80% will be required for successful outcome in the trial.

The changes in 25-OH vitamin D, calcium, phosphate, alkaline phosphatase, and parathyroid hormone, from baseline to end of each phase of study will be studied in all patients to evaluate the

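### The 'without MRSE' group needs no minimum time on statin and is paired on drug and dose but not duration, so some comparators may be labelled before the protocol's own onset window has passed

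*Protocol*

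**What the plan says.** Section 3.0 (Inclusion criteria) admits "Patients placed on statin therapy for the first time in the last year with or without MRSE and with normal CK blood levels". The Subjects paragraph under Objective #1 repeats the one-year limit: "Only patients placed on statin therapy for the first time in the last year with or without MRSE (self-reported and assessed by questionnaires". The exclusion list rules out "Previous use of statins (before the last year", which is again a ceiling. No section states a minimum time on statin for either group. MRSE patients must have had their symptoms begin after the statin was started; no timing rule applies to symptom-free patients.

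Under Functional assessment and blood samples, the comparison is described thus: "A case-control approach will be used to compare patients under statin treatment with and without MRSE". The comparators are "30 patients without MRSE under statin monotherapy (paired for statin and dosage with the MRSE cohort".

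The protocol gives its own view of onset time twice. It justifies the two-month withdrawal by saying that "most statin MRSE as well as structural muscle damage appearance/disappearance occurs within a two month period of statin introduction/withdrawal". Under Objective #2, Trial design, it adds that "patients rarely develop muscle symptoms in less than 2 weeks following statin introduction".

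Time on statin is not among the stratification factors of the randomised phase (MRSE status, 25(OH)D, age and sex). Section 5.0 names one-way ANOVA for continuous variables and plans to compare patients with and without symptoms on percent change.

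**The concern.** The comparator group is defined by the absence of symptoms, and absence is informative only once symptoms have had time to appear. The protocol uses its two-month figure to set the withdrawal period and allows up to two months for rechallenge, but does not apply it to the one group whose label depends on it.

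Two things are at stake, both in the non-randomised contrast of Objective #1:

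- **Label.** A patient symptom-free at three weeks may still develop MRSE. The classification is provisional at baseline testing.
- **Exposure.** Strength, change on withdrawal and muscle histology could each depend on time on drug as well as on symptoms. Pairing on statin and dosage shows that the authors saw a need to balance exposure, but duration is left free. A difference between the groups could therefore partly reflect time on drug. With only 10 comparators biopsied, a few short exposures would weigh most heavily there.

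**Working it through.** The protocol states no figure for time on statin, so there is nothing to reproduce. The check is of the wording, followed by a sizing under stated assumptions.

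**Reading the timing statements together**

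| Time on statin, no symptoms | What the protocol's timing implies |
|---|---|
| Under 2 weeks | Too early: symptoms are rare by then |
| 2 weeks to 2 months | Provisional: onset may already have been possible but is not yet excluded |
| Over 2 months | Most MRSE would have appeared |

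All three rows meet the entry rule.

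**How many comparators are early**

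Inputs: 30 comparators, 10 of them biopsied (Section 3.0, Table 1); windows of 2 weeks and 2 months (Section 3.0). Assumption: start dates uniform over 12 months.

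- Under 2 months: 2/12 = 0.167; 30 × 0.167 = 5.0. P(at least one) = 1 − (1 − 0.167)^30 = 0.996.
- Under 2 weeks: 2/52 = 0.0385; 30 × 0.0385 = 1.15. P(at least one) = 1 − (1 − 0.0385)^30 = 0.69.
- Biopsied comparators under 2 months: 10 × 0.167 = 1.7.
- If the share under two months is instead 5% to 50%: 30 × 0.05 = 1.5 to 30 × 0.50 = 15.

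**How many would later convert**

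Input: MRSE in 10% of users, up to 16% for some statins (Section 2.0). Later converters = 30 × early share × MRSE rate.

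- Uniform starts: 5.0 × 0.10 = 0.5; 5.0 × 0.16 = 0.8.
- Full range: 1.5 × 0.10 = 0.15 to 15 × 0.16 = 2.4.

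Applying the whole rate to early patients is pessimistic, because those already part-way through the window have passed some of the risk.

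**What that does to power (illustration only)**

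The protocol's own power calculation is in an appendix not shown. Inputs: extensor strength change of 22% with SD 43% in the nine preliminary patients (Section 3.0, Preliminary data), taken here as the between-group difference; 60 v 30 patients; two-sided 0.05. Each later converter is assumed to behave like an MRSE patient.

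- Standard error = 43 × √(1/60 + 1/30) = 9.615.
- No misclassification: Φ(22/9.615 − 1.960) = Φ(0.328) = 0.629.
- Diluted difference = 22 × (1 − early share × MRSE rate).

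| Early share | MRSE rate | Difference | Power |
|---|---|---|---|
| 0 | – | 22.0 | 0.629 |
| 5% | 10% | 21.9 | 0.624 |
| 16.7% | 10% | 21.6 | 0.614 |
| 16.7% | 16% | 21.4 | 0.605 |
| 50% | 16% | 20.2 | 0.558 |

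Misclassification alone costs about 0.015 to 0.024 in power under uniform starts. Confounding by time on drug cannot be sized, because the documents give no distribution of duration in either group.

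**The case against.** Several points on the other side stand.

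- **The two-month statement is not a lower limit.** It says that most MRSE appear within two months, so onset can fall anywhere in that period. A reader might infer that everyone under two months is too early to show symptoms. Only patients under about two weeks are, roughly 1 of 30; the rest are provisional.
- **The protocol does not call these patients statin-tolerant.** Its label is that they have no MRSE, which is true of them on the day of testing.
- **The direction is unknown.** A reader might infer that comparators have had less exposure than MRSE patients. The documents do not show it. Both groups come from the same clinic and first-year window, an MRSE patient with symptoms at three weeks qualifies, and symptoms could prompt early presentation.
- **The randomised comparison is safe.** A reader might infer that a first MRSE on rechallenge would distort the vitamin D result. Patients are randomised within MRSE groups, so short-exposure patients fall to either arm by chance, and a first MRSE is a valid event under the self-reported tolerance outcome.
- **Misclassification is small**, as the working shows.
- **Adjustment for duration may be in the statistical analysis plan**, which is not at hand, so its absence from Section 5.0 is not counted here.

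What does not stand is that the contrast is peripheral. Section 5.0 plans the with/without-symptoms comparison, and reduced function in MRSE patients is a primary outcome of Objective #1. Nor can an analysis plan repair the label of a patient enrolled too early; that is fixed by the entry rule.

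**Conclusion.** The point holds as a cheap improvement. The entry rule has a ceiling and no floor, duration is not a pairing factor, and the protocol's own timing makes an early symptom-free patient's label provisional. Under uniform start dates about 5 of 30 comparators are affected (1.5 to 15 for an early share of 5-50%), with about 0.5-0.8 later converting (0.15-2.4).

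The consequence is confined to the non-randomised MRSE v non-MRSE comparison of strength, withdrawal change and biopsies. There, time on drug is uncontrolled, with unknown size and direction. The within-patient withdrawal change in the MRSE cohort and the randomised vitamin D v placebo comparison are not undermined. All counts rest on assumed start dates, and the conversion figures also on the 10-16% rate applying to the comparators.

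**What to change.** In the inclusion criteria, require at least two months of continuous statin use at baseline testing before a patient is classed as without MRSE. Record months on statin for all statin-treated patients, and adjust the MRSE v non-MRSE comparisons for it. Do not add duration as a third hard pairing factor: with a minimum on one side only, an MRSE patient enrolled at three to eight weeks could have no eligible partner. For the same reason, adjustment extrapolates for such patients, so a sensitivity analysis limited to MRSE patients with at least two months on statin would be sensible.

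Under the uniform assumption this takes the expected number of comparators inside the window from about 5 of 30 to 0. No sample size, visit or treatment changes. The cost is that a few comparator candidates wait some weeks and the eligible pool shrinks slightly. The clinic sees over 6000 patients a year, an estimated 85-90% of them on statins, but age, first-year use, low risk and the long exclusion list leave a much smaller pool than that.
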